## Abstract

**Background:**

Ear disease is a major cause of preventable hearing loss and is very common in rural communities, estimated to affect 1.3 million Australians. Rural community pharmacists are well placed to provide improved ear health care to people who are unable to easily access a general practitioner (GP). The purpose of this study is to apply an ear health intervention to the rural community-pharmacy setting in Queensland, Australia, to improve the management of ear disease. The aims are the following: (1) to evaluate the feasibility, potential effectiveness and acceptability of a community pharmacy-based intervention for ear health, (2) to evaluate the use of otoscopy and tympanometry by pharmacists in managing ear complaints in community pharmacy and (3) to evaluate the extended role of rural pharmacists in managing ear complaints, with the potential to expand nationally to improve minor ailment management in rural communities.

**Methods/design:**

This is a longitudinal pre- and post-test study of a community-pharmacy-based intervention with a single cohort of up to 200 patients from two rural community pharmacies. Usual care practices pertaining to the management of ear complaints will be recorded prior to the intervention for 8 weeks. The intervention will then be piloted for 6 weeks, followed by a 12 month impact study. Patients aged > 13 years presenting to the pharmacies with an ear complaint will be invited to participate. Trained pharmacists will conduct an examination including a brief history, hearing screening, otoscopy and tympanometry assessments. Patients will be referred to a general practitioner (GP) if required, according to the study protocol. Patients will complete a satisfaction survey and receive a follow-up phone call at 7 days to explore outcomes including prescribed medications and referrals. Pharmacists and GPs will complete pre- and post- intervention interviews. Patient, pharmacist and GP data will be analysed using descriptive statistics and thematic analysis for the qualitative data.

**Discussion:**

This study will demonstrate the implementation of a screening and referring ear health intervention in rural community pharmacy. Feasibility, potential effectiveness and acceptability of the intervention will be assessed.

**Trial registration:**

Australian and New Zealand Clinical Trial Registry Number: ACTRN12620001297910.

**Supplementary Information:**

The online version contains supplementary material available at 10.1186/s40814-021-00856-6.

## Background

Ear care is recognised as important for the health of the population [1]. Ear disease is increasing globally with the World Health Organisation (WHO) proposing that by 2050 we can expect 900 million people to have disabling hearing loss, twice that of 2019 [2]. In Australia, more than 1.3 million people are living with a hearing condition that could have been prevented [3]. In rural and remote communities, the prevalence rate of middle ear diseases is as high as 50% in children under 3 years of age, double the prevalence recognised by WHO as a ‘massive public health problem’ [1, 2]. As well as the health consequences, unmanaged ear disease correlates with poor educational, social and behavioural outcomes [1].

Access to trained health care providers and a lack of infrastructure and supplies have been recognised as major challenges to providing ear care internationally [1]. There is currently a shortage of health care workers in rural and remote communities able to provide ear health care, which is predicted to worsen in the future [4]. Despite these shortages, there have been a number of innovative models of care developed to utilise consistently accessible health care professionals such as pharmacists to improve ear care [5]. A scoping review of community pharmacist interventions in ear health identified eight studies, whereby pharmacists provided a targeted ear health service, including hearing screening (4 in Australia), an otoscopy pilot study (1 in England) and pharmacy-based ear clinics (1 in USA; 2 in England) [5].

Pharmacists are trusted and accessible health professionals, who are motivated to meet local community needs [6]. Internationally, rural pharmacists are providing innovative models of care and working at expanded scopes of practice to better meet health needs [7]. Pharmacists, consumers and health professionals living in rural and remote locations in Australia are supportive of pharmacists expanding their service delivery to improve patient outcomes [8–10]. Rural pharmacists in Australia work in a unique setting with complex patients and limited access to health services and the potential for them to improve ear health care is unknown. A new pilot programme was developed to explore the impact of a pharmacist ear care intervention on patient-related outcomes.

Pilot and feasibility studies are an important step in the development of successful interventions for health [11]. There is emerging acknowledgement of the value of pilot studies to better understand the conduct and applicability of an intervention to allow the results to be better applied to patient care [11].

This paper describes the research protocol of the pilot, LISTEN UP (Locally Integrated Screening and Testing Ear aNd aUral Programme), a rural community pharmacy-based intervention to improve the management of ear health in the community in Australia.

### Research aims

This study aims to: (1) explore the feasibility, potential effectiveness and acceptability of a community pharmacy-based intervention for ear health, (2) evaluate the use of otoscopy and tympanometry by pharmacists in managing ear complaints in community pharmacy and (3) evaluate the extended role of rural pharmacists in managing ear complaints, with potential to expand nationally to improve ear care minor ailment management in rural communities.

## Methods and design

### Study design and setting

This is a longitudinal pre- and post-design study of a community-pharmacy-based intervention piloted in two rural community pharmacies in Queensland, Australia. Co-design has been applied to this study with stakeholder, health professional, pharmacist and consumer perspectives from previous research utilised in conjunction with community consultation to inform the design of this study [8–10]. Prior to the intervention, participating pharmacies will collect usual care data for 8 weeks beginning November 2020. The intervention will then be piloted for 6 weeks at each pharmacy and then refinement and improvements will be made before the longitudinal impact study is conducted for 12 months.

### Ethics approval

This project has been approved by the Human Research Ethics Committee, James Cook University (Reference number: H8187).

### Pharmacies

#### Pharmacy eligibility criteria

Community pharmacies that meet the following criteria are eligible to participate as a study site:
Participating pharmacists must hold unconditional registration with the Australian Health Practitioner Regulation Agency (AHPRA) [12].Maintain accreditation standards for quality assurance under the Quality Care Pharmacy Programme (QCPP) [13].Have a private counselling area within the pharmacy that is separated from the common pharmacy counter, where one-to-one consultations can be conducted.Have a high daily ‘walk-in customer’ number of more than 100 customers per day.Have suitable information technology including a computer with internet access, printer and scanner.Are classified as rural or remote by the Modified Monash Model classification system categories 4-7 [14].Are located in Queensland, Australia, due to COVID-19 interstate restrictions around travel for training.

#### Recruitment of pharmacies

Pharmacies who have participated in earlier research on rural expanded pharmacy practice will be invited to express an interest to participate in the LISTEN UP. Those pharmacies who are interested will be phoned by the principal investigator to provide further explanation of the study and obtain consent. Two pharmacies will be enrolled in the study. Each pharmacy will be linked with at least one participating general practitioner. An invitation to participate with an information sheet and informed consent form will be provided to each pharmacist at the participating pharmacies and each GP at the participating general practices.

#### Pharmacist training

Each participating pharmacist will undertake nationally credentialed training in ear health including otoscopy and tympanometry. This training will be mixed mode with online and face-to-face components. The training includes 55 h of online training and two full days of workshops and is provided by the Benchmarque Group [15]. The training will include the following units of competencies: EHHPEH002—promote, educate and manage ear health; EHHAEH001—assess ear health; EHHPEA004—paediatric and TYMPTY001—perform tympanometry.

Only pharmacists who have successfully completed the required training will be eligible to participate in the study. Completed certificates of training will be provided to the principal investigator.

All training, including training materials will be consistent with national standards and will be tailored to suit the needs of community pharmacists. In addition, pharmacists will be provided with a list of recommended supplemental readings and resources. A member of the research team who is a pharmacy academic will also provide face-to-face and virtual training to the pharmacists on documentation processes for the project.

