### Data saturation

Total population sampling will be conducted in this study. We will attempt to interview all GPs and pharmacists by inviting them to participate in an interview three times. In addition, all participants will receive a follow-up phone call four times, including at least one out of normal business hours, in an attempt to ensure as many as possible participants receive the follow-up phone call.

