#### Study measurements

The study measurements collected in the intervention include pharmacist views, pharmacist recommendations, GP views and patient views. There measurements are aligned to the primary and secondary outcomes of the study (Table 2).

**Table 2 Tab2:** Summary of study measurements aligned to study outcomes

Measurement	Instruments	Pre-study	During study	Post-study	Primary outcome	Secondary outcome
Pharmacist views	Semi-structured interview	X		X	1a	1, 2
Pharmacist recommendations	Service summary document		X			1, 2, 3
GP views	Semi-structured interview	X		X	1c	1, 2
Patient views	Satisfaction Survey			X	1b	1, 2
Patient views	Semi-structured interview			X	1b	1, 2, 3

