##### Primary

To evaluate the feasibility, acceptability and potential effectiveness of a community pharmacy-based intervention for ear health by exploring:
Pharmacist views of:
i.Pharmacist capacity and competence to provide the intervention (motivation, confidence, competence, experience of training, capacity (workflow/workload))ii.Patient acceptanceiii.Pathway to GP service (timeliness of appointment, GP staff attitudes)Patient views of the service in terms of access, alternative health care options, satisfaction and willingness to pay (confidence/acceptance of pharmacist service, referral process, timeliness of pharmacists consult/GP consult).GP views on appropriateness of pharmacist referrals, collaborative care with pharmacists (use of telehealth).To evaluate the use of otoscopy and tympanometry by pharmacists to improve specificity of ear condition management in community pharmacy by comparing:
Usual care data with intervention data pertaining to pharmacist recommendations.Pharmacist recommendations on the patient service summary record compared to GP prescriptions and referrals described by patients at the 7-day follow-up phone call.Patient acceptance of pharmacists performing examinations with an otoscope and tympanometer.

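### Training completion is a condition of being in the study, so the "experience of training" part of primary outcome 1a(i) may come from completers only

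*Protocol article*

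**What the plan says.** Under Recruitment of pharmacies, two pharmacies are enrolled and consent is sought from every pharmacist in them: "An invitation to participate with an information sheet and informed consent form will be provided to each pharmacist at the participating pharmacies".

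Under Pharmacist training, the load is set out: "The training includes 55 h of online training and two full days of workshops". The section then adds the eligibility rule, "Only pharmacists who have successfully completed the required training will be eligible to participate in the study", and has completion certificates sent to the principal investigator.

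Under Study outcomes, Primary, the first objective is "To evaluate the feasibility, acceptability and potential effectiveness of a community pharmacy-based intervention for ear health by exploring" three sets of views: those of pharmacists (1a), patients (1b) and GPs (1c). The first pharmacist item, 1a(i), concerns capacity and competence to provide the intervention and lists "motivation, confidence, competence, experience of training, capacity (workflow/workload".

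Table 2, under Study measurements, gives the semi-structured interview, pre- and post-study, as the only instrument for 1a. On who is interviewed, the Data saturation section says: "We will attempt to interview all GPs and pharmacists by inviting them to participate in an interview three times".

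**The concern.** A pharmacist who begins a course of this length and stops, or does not pass, has first-hand experience of the training. If that pharmacist is not a study participant, the item on experience of training is conditioned on success at the thing being asked about. Completers can still criticise the course, but the people for whom it proved unworkable are the ones not heard.

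This matters because feasibility belongs to the first primary objective, and because the third aim and the second secondary outcome look towards a national model. The training load is a plausible barrier to such an expansion. None of the outcomes listed in the article counts how many pharmacists started and finished, and the limitations section does not mention this selection. The point concerns loss at the training step. It does not concern later withdrawal, or pharmacists who never took up the offer.

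**Working it through.** The plan gives no figure on this point to reproduce. Its one sample-size calculation is for patients and has no bearing here. The check is to set the sections side by side and follow one pharmacist who consents, starts training and does not finish.

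1. **Consent.** Recruitment of pharmacies: the invitation and consent form go to each pharmacist at both sites. This pharmacist is included.
2. **Eligibility.** Pharmacist training: without completion, the pharmacist may not take part in the study. The sentence does not confine itself to examining patients. This pharmacist is excluded.
3. **What is measured.** Primary outcome 1a(i) asks about five things: motivation, confidence, competence, experience of training, and capacity. Its lead-in is about providing the intervention. Capacity in the sense of workflow and workload is therefore mainly a matter for those who deliver the service. Experience of training is the item that a non-completer can speak to directly.
4. **Where it comes from.** In Table 2, 1a is fed by the pharmacist interview only. The service summary document is aligned to secondary outcomes only, so no second source would pick up non-completers.
5. **Who is interviewed.** Data saturation says all pharmacists, without defining the set. Read with step 2 it means eligible pharmacists. Read with step 1 it means all who consented. The text does not settle which.
6. **Timing.** Study measurements and outcomes places the first interview before the study begins, to explore expected feasibility, and does not give its order relative to training. If it comes before training, it cannot record experience of training. If it comes after, the rule in step 2 already applies. In either case no text gives a non-completer a post-study interview, so that person also drops out of the comparison of views before and after.

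**Illustration, on assumed numbers.** Let m pharmacists start training and k not finish. Under the literal reading, the share of those with experience of the training who are not heard is k/m. The protocol gives neither m nor k, so the range below is an assumption (m from 4 to 10, k from 0 to 3):

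| Starters m | k = 0 | k = 1 | k = 2 | k = 3 |
|---|---|---|---|---|
| 4 | 0/4 = 0% | 1/4 = 25% | 2/4 = 50% | 3/4 = 75% |
| 6 | 0/6 = 0% | 1/6 = 17% | 2/6 = 33% | 3/6 = 50% |
| 8 | 0/8 = 0% | 1/8 = 12.5% | 2/8 = 25% | 3/8 = 37.5% |
| 10 | 0/10 = 0% | 1/10 = 10% | 2/10 = 20% | 3/10 = 30% |

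These are shares of people not interviewed. They are not estimates of bias, and nothing in the document indicates which cell applies. They show only that in a group this small a single missing voice can be a sizeable part of the data.

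**The case against.** The strongest reply is that the eligibility sentence was meant as a competence requirement for delivery. It stands in the training section next to the collection of certificates. The same section calls pharmacists participating before they have trained, and the abstract has trained pharmacists carrying out the examinations. On that reading consent comes first, training follows, and completion only opens the way to seeing patients. Data saturation adds total population sampling with three invitations, and no sentence limits interviews to certificate holders. A pharmacist who later stops may even have been interviewed beforehand about expected barriers.

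Much of this stands as evidence that the text is not consistent. It does not remove the point, because the sentence itself says participation in the study and no section places non-completers in the interview set. If delivery-only was the intention, the rewording below simply records it.

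A second reply is that counts of starters and completers are participant-flow detail that a condensed article may leave to the full protocol. That is fair, and the missing count alone would be no finding. What is challenged is a stated eligibility rule that cuts across a stated primary outcome. The count is part of the remedy.

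A third reply is that pharmacists who finish can describe the burden perfectly well. They can, so criticism of the training is not suppressed. It is only drawn from the more successful group.

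**Conclusion.** The point holds in a limited form. As written, the eligibility rule leaves consented pharmacists who start but do not finish training out of the interviews that supply outcome 1a, and the sentence on interviewing all pharmacists does not clearly restore them. Reported experience of training would then rest on completers and may be too favourable.

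The size cannot be computed. The number of pharmacists and any non-completion are unknown, and the effect is nil if everyone finishes. The conclusion assumes that the eligibility sentence is followed literally and that at least one starter does not complete.

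Two stronger readings are tempting but not supported:

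- A reader might infer that the feasibility verdict as a whole is conditioned on success. It is not: 1a(i) is one part of the pharmacist views, and feasibility is also explored through patient views (1b) and GP views (1c).
- A reader might infer that the plan would report every pharmacist as able to take the service on when the true share is lower. It would report no such proportion, because the Data analysis section has the interviews analysed thematically.

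**What to change.** Three small changes would settle it:

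1. In Pharmacist training, reword the rule so that successful completion is required to deliver LISTEN UP consultations, rather than to take part in the study. The training requirement for anyone who examines patients stays as it is.
2. In Data saturation, state that all consented pharmacists who start training are invited to interview, including those who do not complete, who are invited when they stop.
3. Alongside outcome 1a, report the numbers of pharmacists consented, started and completed, with reasons for non-completion. Consent forms and completion certificates are already part of the study procedures, so the new items to record are who started and why anyone stopped.

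The cost is a few sentences of text and a few extra interviews at most. Reported views of training may turn out less favourable. If everyone completes, the counts will show it and the question is closed.

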### General practitioners (GPs)

#### General practitioner eligibility criteria

GPs that meet the following criteria are eligible to participate in the study:
Hold unconditional registration with the Australian Health Practitioner Regulation Agency (AHPRA).Have capacity to provide timely appointments (within 48 h) for participants referred to them for review.Have suitable information technology provisions including a computer with internet access, printer and scanner.Are classified as rural or remote by the Modified Monash Model classification system categories 4-7 [14].Are located in Queensland, Australia, due to COVID-19 interstate restrictions around travel for training.

#### Recruitment of GPs

At each pharmacy location, all GP practices within a 25-km radius will be invited to participate in the study.

### Participants

#### Sample size

The sample size was calculated using the formula *n* = Z^2^*P* (1-*P*)/*d*^2^, where n=sample size, Z is the critical value of the normal distribution at α/2 for a confidence level of 95% where α is 0.05 and the critical value is 1.96, *P* = expected prevalence or proportion = 0.14 (14%) and d = precision = 0.05 (5%) [16]. To our knowledge, there is no published community pharmacy-based ear health interventions of similar nature, therefore no standard reference could be applied to accurately determine prevalence required to calculate the sample size. However, we have calculated a sample size based on data from the Australian Government Department of Health, which estimates 14% of Australians suffer from hearing loss [3]. Therefore, *n* = 185 + 10% for missing data = 203 participants.

Given the calculated sample size, it is expected that each of the two participating pharmacies would recruit 100 patients into the study during the impact study. The duration of the project will be extended for up to 12 months to ensure adequate patient participant numbers to power the study.

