### Intervention participants

Participants' temperature will be measured in the waiting area, if > 37.5 Celsius COVID-19 precautions will be implemented and additional personal protection equipment (PPE) applied, including face mask, gloves and face shield. Pharmacists will conduct the consultation with eligible consenting participants in a private consultation space. Pharmacists will then document a brief history of the ear complaint including symptoms, duration and treatments tried by the patient on a template service summary document (Appendix 1) provided to them. Pharmacists will then examine the ears using otoscopy and tympanometry. If the complaint is hearing related, pharmacists will perform a hearing screening test using the *Sound Scouts* application [17]. *Sound Scouts* is an application based hearing check that can be used in persons over the age of 4 years to detect conductive hearing loss, sensorineural hearing loss and difficulties listening in noise [17].

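### The sample size is calculated for the national prevalence of hearing loss, so the ±5-point precision is established for no planned outcome and the claim of power has no basis

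*Protocol article*

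**What the plan says.** The Sample size section uses the formula for estimating one proportion, n = Z²P(1−P)/d², at a "confidence level of 95% where α is 0.05 and the critical value is 1.96", with P = 0.14 and d = 0.05. It explains that, for lack of a comparable pharmacy study, "no standard reference could be applied to accurately determine prevalence required to calculate the sample size". It therefore borrows P from a government source that "estimates 14% of Australians suffer from hearing loss". The result is given as "185 + 10% for missing data = 203 participants", with about 100 patients expected from each of two pharmacies. The project may run for up to 12 months "to ensure adequate patient participant numbers to power the study".

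Elsewhere in the same article:

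- Participant eligibility criteria: participants are walk-in customers seeking help for an ear complaint.
- Intervention participants: "If the complaint is hearing related, pharmacists will perform a hearing screening test".
- Study outcomes, Primary: the outcomes are pharmacist, patient and GP views, and two comparisons of recommendations together with patient acceptance of the examinations. The first comparison is "Usual care data with intervention data pertaining to pharmacist recommendations". The second sets pharmacist recommendations against the GP prescriptions and referrals that patients report at 7 days.
- Data analysis: descriptive statistics and frequencies for surveys and service records, and thematic analysis for interviews.

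**The concern.** A precision-based sample size has meaning only for the quantity whose proportion goes into the formula. Here that quantity is the share of the general population with hearing loss, which appears in neither outcome list. The study could not estimate it: entry depends on having an ear complaint, and only some participants have their hearing tested. The ±5 points is thus attached to something the study will not report, and nothing in the article carries it over to what the study will report.

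The wording about power adds a second claim. A confidence-interval width for one proportion is not power, and the article names no comparison for which power could be calculated. At stake is how the results are read. Satisfaction and acceptance percentages, and the two comparisons of recommendations, could be taken as precise to within 5 points or as adequately powered, and the plan shows neither.

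**Working it through.** **Inputs (Sample size section).** Z = 1.96, P = 0.14, d = 0.05, 10% added for missing data, planned recruitment 2 × 100 = 200.

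**Reproducing the plan's figure.** n = 1.96² × 0.14 × 0.86 / 0.05² = 3.8416 × 0.1204 / 0.0025 = 185.01, stated as 185. Then 185 × 1.10 = 203.5, stated as 203. Both reproduce, so the difficulty is the input and not the arithmetic.

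**Where ±5 points holds with 185 patients.** The half-width is 1.96 × √(p(1−p)/n). Requiring it to be at most 0.05 gives p(1−p) ≤ 185 × 0.0025 / 3.8416 = 0.1204, that is p ≤ 0.14 or p ≥ 0.86, with all 185 contributing.

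**Half-width for a full-sample proportion, in percentage points.**

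| True proportion | n = 185 | n = 200 |
|---|---|---|
| 14% or 86% | ±5.0 | ±4.8 |
| 20% or 80% | ±5.8 | ±5.5 |
| 30% or 70% | ±6.6 | ±6.4 |
| 50% | ±7.2 | ±6.9 |
| 90% | ±4.3 | ±4.2 |

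If 10% of 200 are missing, 180 remain and the half-width at 50% is ±7.3. To reach ±5 at 50% would take 3.8416 × 0.25 / 0.0025 = 384.2, that is 385 patients.

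**Usual care versus intervention.** This is a difference between two groups, with half-width 1.96 × √(p(1−p)(1/n₀ + 1/185)) if both proportions are near p. The term 1/n₀ always adds to the width, so at a given p it is wider than the single-proportion figure. The article gives no expected number of usual-care records for the 8 weeks. As an illustration only, at p = 0.5:

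- n₀ = 30: ±19.3 points
- n₀ = 100: ±12.2 points
- n₀ = 200: ±10.0 points

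**Pharmacist versus GP.** Only patients who saw a GP and were reached at 7 days can contribute. The article gives no expected number. As an illustration only, if half of 185 were evaluable (about 92), the half-width would be ±10.2 at 50% and ±7.1 at 14%.

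**Power.** A power calculation needs a hypothesis, an effect size and a test. The Sample size section gives none of these, and the Data analysis section is descriptive. There is nothing to compute.

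**The case against.** The best defence is that this is an uncontrolled pilot, described as small under Limitations, with descriptive analysis. The article says openly that no reference existed and that a proxy was used. That stands as an explanation, and a precision-based size is acceptable for a pilot. It does not link the proxy to anything the study reports. Hearing loss is one of the complaint categories in the usual-care record, and screening results are recorded, but neither is an outcome and screening does not cover all patients.

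The second defence is that some outcomes may well meet ±5 points. This also stands. A reader might infer that the stated precision fails for every planned outcome. The documents do not support that, because they give no expected proportion for any outcome. Satisfaction or acceptance of 90% across 185 patients would give ±4.3.

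A reader might also infer definite figures for the two comparisons, or predict that the primary intervals will be several times wider than ±5. Those figures would rest on assumed numbers of usual-care records and assumed referral, attendance and contact rates. Usual-care records are non-identifiable and carry no stated consent step, so the enrolment rate need not predict their number. Likewise, any figure for clustering would rest on an assumed intraclass correlation, since none is given.

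**Conclusion.** The concern holds in this form: the ±5-point precision is established for no planned outcome, which is a weaker statement than that it is met by none. For a full-sample patient proportion the half-width with 185 patients lies between ±5.0 and ±7.2 when the true value is between 14% and 86%, and is below ±5 outside that range. These figures need only the plan's own formula and assume that all 185 contribute and that observations are independent.

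The two comparisons of recommendations will be less precise than a full-sample proportion of the same size, one because it is a difference and the other because it uses a subset. By how much cannot be settled from the article. The claim of power is without basis. The consequence is limited to what the study says about its own precision: neither the recruitment target nor the analysis is undermined.

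**What to change.** Keep the target of about 200 patients and rewrite its justification in the Sample size section:

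- Drop the 14% hearing-loss input.
- State that about 200 patients give a 95% half-width of about ±7 points for full-sample patient proportions, using the conservative P = 0.5.
- State that the usual-care versus intervention comparison and the pharmacist versus GP comparison will be less precise, and why. The sponsor should give their half-widths from its own expected counts: usual-care records in 8 weeks, and patients who see a GP and are reached at 7 days.
- Note that all these figures ignore clustering within two pharmacies.
- In the sentence that ends "to ensure adequate patient participant numbers to power the study", replace the reference to power with *to reach the target precision*.

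The cost is one rewritten paragraph and a less favourable stated precision. No extra patients are needed, and the outcomes and analysis do not change.
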